#### Usual care regimen

Subjects randomized to the waitlisted control group will receive no formal intervention, but will continue to have standard post-treatment clinic visits according to their treatment plans. Additionally, to avoid possible overlap (contamination) with components of the MBSR program, the investigators will specifically ask subjects in the waitlisted control group not to start mindfulness-based practice during the study period.

MBSR intervention will be offered to each usual care subject after 6 months follow-up. They will be provided with a brief orientation to MBSR (BC), a manual on the program, and a 2-month practice class after post-assessment.

### Outcomes

#### Expected outcomes

1) Improvement in mental health, QOL, and meditation adherence in the MBSR intervention group, which is generalizable to East Asia’s growing population of BC survivors. As our 2010 commentary in *Science* states [36], the age of BC incidence among East Asian women tends to be substantially younger than that of Caucasian women. Therefore, good mental health among this population of BC survivors also means a labor productivity gain for China’s shrinking labor force. 2) A lifestyle-oriented, non-pharmacological psychological intervention protocol to help BC survivors to self-control their stress, which will become easier to access among low-income communities thanks to the training program in our study.

The following instruments would be used to measure the outcome and the possible mediators.

#### Practice quantity

A meditation calendar will be provided to participants to document the daily number of minutes spent in formal meditation practice, and the participants are expected to document this figure at the end of each day during the intervention. Calendars will be collected at the end of the intervention, following the practice of mindfulness intervention in smoking abstinence [37].

#### Practice quality

The 7-item mindfulness practice quality questionnaire [38], which measures the dimension of perseverance and the dimension of receptivity, will be conducted at each session following formal meditation practice.

#### Psychological assessment

Several psychometric scales will be used.Self-rating Depression Scale (SDS) [39]. SDS is a 20-item instrument with a 4-point Likert scale. Higher scores indicate higher depression level.Self-rating Anxiety Scale (SAS) [40], a 20-item instrument with a 4-point Likert scale. Higher scores indicate higher anxiety level.Mindful attention awareness scale (MAAS) [41], which includes a 15-item instrument designed to assess the frequency with which an individual is openly attentive to and aware of present events and experiences. The scale assesses mindfulness of both internal states (e.g., emotions) and overt behaviors (e.g., attention to tasks and social interactions) on a 6-point Likert scale. Higher scores indicate higher mindfulness.Quality of Life Index – cancer version III [42], which evaluates QOL in terms of an individual’s satisfaction or dissatisfaction with aspects of life that are important to him/her. The Quality of Life Index measures life satisfaction in four domains: health and functioning, socioeconomic, psychological/spiritual, and family. It consists of two parts with 34 items, using a 6-point Likert scale. Part I measures satisfaction within each identified domain, whereas part II measures the perceived importance of each item. Satisfaction scores are weighted by importance.

#### Compliance level with medication treatment

Morisky Medication Adherence Scale, 8-item version (MMAS) [43], which will be modified to assess subject’s medication adherence. It has 8 items and scores range from 0 to 8. Scores of <6 indicate low, scores of 6–7 indicate medium, and a score of 8 indicates high adherence.

#### Compliance level with intervention

Questionnaire items will be developed to record subjects’ MBSR practice at home, including practice types, number of minutes, and so on.

#### Demographic and health history form

Demographic information will be collected, including age, marital status, education, and employment status. Medical records will be reviewed to obtain information regarding age at BC diagnosis, cancer pathology, past and current cancer treatment, and patient’s compliance with treatment. At each assessment, a health history form will be completed by the participants, including questions related to presence of other medical conditions or diseases, current use of prescription and non-prescription medications and supplements, and occurrence of recent illness.

### Sample size

Based upon an MBSR study among BC survivors where the intervention group had significantly better aggregated physical health outcome as measured by SF-36 (50.3 among MBSR subjects vs. 46.9 among the control group) [44], we used STATA 12.0’s power calculator to find that our two-group, three-follow-up design needs 195 participants for each of the two groups, i.e., 390 subjects in total. Assuming an attrition rate of 10 % (attrition rate here means the percent of people who drop out from the study due to moving away, death, etc.), we concluded that we need to recruit a sample of 429 BC survivors at baseline.

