#### Implementation

Following completion of their hospital treatment, BC survivors return home. As part of the newly launched cancer registry system, each community health service center (CHSC) in Shanghai collects BC survivors’ detail information in order to ensure follow-up and to analyze mortality and morbidity rates. Based on the patient lists from CHSC, we will contact these BC survivors directly to recruit potential participants. All participants who are willing to attend this trial will be requested to submit a signed informed consent. After that, all participants who provide an informed consent will then complete a baseline questionnaire for psychometric assessment (Time 0), with the help from investigators. Information about demographic background and health status will also be collected and later verified by a review of hospital charts.

The immediate intervention group will start the program within 2 weeks of randomization. Two certified MBSR psychotherapists will be hired to implement a standard MBSR intervention. Members of the research team will attend each MBSR session to ensure that intervention standards are met.

All subjects will be reassessed after the intervention group completes half of the program (4 weeks into the intervention, Time 1), 8 weeks later (Time 2), and at 6 (Time 3) and 12 months (Time 4) from the beginning of the intervention. Participants in the control group will be given the opportunity to complete the MBSR program after 6 months follow-up. Eight investigators will be in charge of these follow-ups by telephone.

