### Statistical methods

We will compare the outcome variables (SDS, SAS, MAAS, Quality of Life Index, and MMAS) between the two groups using the χ^2^ test for categorical variables and Student t or Wilcoxon tests for continuous variables. Analysis of covariance (ANCOVA) will be conducted to assess whether MBSR is related to changes between baseline and after 8 weeks of intervention in relation to psychological status, QOL, and compliance behaviors.We will use a structural equation model [45] to examine the intervening role of mindfulness enhancement on improving mental health, QOL, and compliance with medical treatment. Mediation analysis, as implemented in MPlus 7.11, will be used to analyze the causal pathway from MBSR intervention to health outcomes through mindfulness enhancement.We will use a random-effects repeated measures analysis [46] to examine the impact of MBSR intervention on health outcomes, compliance behavior, adjusting for confounding variables (age, education, household income, occupation, previous cancer history, and household registration status: Shanghai vs. non-Shanghai). The repeated measure analysis approach accounts for the same individual’s different outcome measures across different points in time without assuming either linear or curvilinear growth pattern. Cronbach alpha’s will be computed to determine the internal consistency of our outcome measures. Using this approach (as implemented by the PROC MIXED and PROC GLIMMIX modules in SAS 9.0), we have published an article analyzing a famous randomized controlled trial of lung cancer screening, which shows a behavioral differential between the two trial arms [47].

The relationship between methods used for each hypothesis is shown in Table 1.

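### The 195 per group is sized on an SF-36 physical-health difference over three follow-ups, but the primary hypothesis is tested on other scales by an 8-week ANCOVA, so the stated size does not establish power for that analysis

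*Protocol article*

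**What the plan says.** Sample size bases the calculation on an earlier MBSR study in which "the intervention group had significantly better aggregated physical health outcome as measured by SF-36" ("50.3 among MBSR subjects vs. 46.9 among the control group"). It then reports that "our two-group, three-follow-up design needs 195 participants for each of the two groups", "i.e., 390 subjects in total" before attrition. It names the software but gives no SD, alpha, power, between-visit correlation or repeated-measures method.

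The instruments under Outcomes, and the outcome variables listed in Statistical methods, are SDS, SAS, MAAS, Quality of Life Index and MMAS. SF-36 is not among them. Primary Hypothesis 1 concerns mental health, quality of life and medication compliance.

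On timing, Statistical methods says: "Analysis of covariance (ANCOVA) will be conducted to assess whether MBSR is related to changes between baseline and after 8 weeks of intervention". Table 1 gives Primary Hypothesis 1 to bivariate analyses and ANCOVA, and gives repeated measures analysis to the secondary hypothesis. Under Implementation, follow-up is at 4 weeks, at 8 weeks, "and at 6 (Time 3) and 12 months (Time 4) from the beginning of the intervention". Controls are offered MBSR after the 6-month assessment.

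**The concern.** A sample size calculation supports a test only if it uses that test's endpoint and design. Here neither matches.

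- **Endpoint.** A 3.4-point difference in SF-36 aggregated physical health cannot be turned into power on a depression, anxiety, life-satisfaction or adherence score without an SD and a target difference for that score. The article gives neither.
- **Design.** A calculation that averages three follow-ups per woman works with a smaller variance than a test at one visit. If 195 depends on that reduction, it is too few for the same power at 8 weeks alone.

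At stake is whether the planned size has any stated justification for the trial's main question. The article says that the trial had not begun, so the paragraph could still be corrected before recruitment.

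**Working it through.** **1. Can 195 be reproduced?** No. The only inputs given are the difference of 3.4, three follow-ups and n = 195. Assuming a plain one-visit comparison, two-sided 5%, and solving for the SD:

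SD = 3.4 / (1.960 + z_power) × √(195/2)

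- 80% power: 3.4 / 2.802 × 9.874 = 11.98
- 90% power: 3.4 / 3.242 × 9.874 = 10.36

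If the mean of three follow-ups was used, with common correlation r, the variance is multiplied by (1 + 2r)/3. The implied SD at 80% power then runs from 16.4 (r = 0.3) to 12.9 (r = 0.8). The article states no SD that would tell these readings apart, so 195 can be neither confirmed nor refuted.

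**2. If 195 took credit for three visits, what is left at one visit?** Assumptions: two-sided 5%, common correlation r from 0.3 to 0.8, the same effect at every visit. The variance factors are:

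- Follow-up mean: three visits (1 + 2r)/3; one visit 1
- Baseline-adjusted ANCOVA: three visits (1 + 2r)/3 − r²; one visit 1 − r²
- Change score: three visits (1 + 2r)/3 + 1 − 2r; one visit 2 − 2r

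With R = one-visit factor / three-visit factor, the one-visit test needs 195 × R per group, and its power with 195 is Φ[(1.960 + z_power)/√R − 1.960].

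| Method | R (r = 0.3 to 0.8) | Per group at one visit | Power, if planned at 80% | Power, if planned at 90% |
|---|---|---|---|---|
| Follow-up mean | 1.88 to 1.15 | 366 to 225 | 53% to 74% | 66% to 86% |
| ANCOVA | 2.05 to 1.59 | 401 to 310 | 50% to 60% | 62% to 73% |
| Change score | 1.50 | 293 | 63% | 75% |

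Example, ANCOVA at r = 0.5: R = 0.75 / 0.4167 = 1.80; 195 × 1.80 = 351 per group; power = Φ(2.802/1.342 − 1.960) = Φ(0.128) = 55%.

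**3. If 195 took no credit for repeated visits.** R = 1 and no power is lost. The reference to three follow-ups then describes something that the calculation did not use.

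**4. What 195 per group detects at 8 weeks, in SD units.** Unadjusted: (1.960 + z_power) × √(2/195), which is 0.284 SD at 80% power and 0.328 SD at 90%. With baseline-adjusted ANCOVA the 80% figure is multiplied by √(1 − r²):

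- r = 0.3: 0.284 × 0.954 = 0.27
- r = 0.5: 0.284 × 0.866 = 0.25
- r = 0.7: 0.284 × 0.714 = 0.20

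All of these are before any allowance for clustering within MBSR classes of 20 to 30.

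**The case against.** Three points can be made for the plan.

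**The visit count.** A reader might infer that three follow-ups contradicts the four in the schedule. The documents do not support that. Controls are offered MBSR after 6 months, so exactly three follow-ups (4 weeks, 8 weeks, 6 months) compare the arms before crossover. The mismatch is between three visits and the one visit in the ANCOVA.

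**The primary analysis.** Statistical methods gives no visit for the bivariate tests. It also describes the random-effects model as examining the effect of MBSR on health outcomes and compliance, which covers the domains of Primary Hypothesis 1. Table 1 is itself loose: it cites Objectives 3 and 4, whereas the main-study list appears to hold three. This weakens the claim that only one visit matters. Still, Table 1 assigns the repeated-measures model to the secondary hypothesis and ANCOVA to Primary Hypothesis 1, and the ANCOVA sentence fixes 8 weeks.

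**Power.** A reader might infer that the trial is underpowered, or that a null result could not be interpreted. Neither follows. An article may leave SD, alpha, power and correlation to the full protocol, and 195 may have been a one-visit calculation. A null result can be read from its confidence interval whatever the planning rationale was.

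The Quality of Life Index does have a health and functioning domain, so the SF-36 result is not wholly remote. It is nevertheless a different, importance-weighted satisfaction score and cannot stand in for the SF-36 scale. An analysis plan could supply missing parameters, but it could not make SF-36 a measured outcome without departing from this text.

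**Conclusion.** The point holds in this form: the justification for 195 per group uses an endpoint that the trial does not measure and a number of visits that the ANCOVA for Primary Hypothesis 1 does not use. It therefore does not establish power for that analysis on SDS, SAS, Quality of Life Index or MMAS. The scale mismatch is certain from the text. The design mismatch rests on Table 1 read with the ANCOVA sentence.

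The effect on power is conditional. Under the assumptions in step 2 it ranges from no loss, if no credit was taken for repeated visits, to one-visit power of about 50% to 74% for an 80% plan (62% to 86% for a 90% plan). The documents do not say which case applies. Nor do they allow a judgement on whether a detectable effect of 0.20 to 0.28 SD is adequate, because they give no SD or target difference for any measured scale.

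**What to change.** Keep the recruitment target and remove SF-36 as its basis. Designate one measured scale as primary. Then state what 195 per group detects on it at 8 weeks with the planned analysis, at two-sided 5% and 80% power: 0.28 SD unadjusted, or about 0.27, 0.25 and 0.20 SD with baseline-adjusted ANCOVA at r = 0.3, 0.5 and 0.7, before class clustering. Convert this to points with a sourced SD for that scale. The cost is a rewritten paragraph and the choice of a primary scale; no extra patients are needed.

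Alternatively, make the repeated-measures model over 4 weeks, 8 weeks and 6 months the analysis for Primary Hypothesis 1, amend Table 1 and Statistical methods, and state the assumed correlation along with the SD and target difference on the chosen scale. This agrees with the three follow-ups in the sizing. Its drawback is that the 4-week visit falls mid-programme, so an average over visits may understate the effect of the full course. The 8-week contrast should be reported from the same model.

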**Methods:**

A randomized, waitlist-controlled clinical trial will be conducted. Based on our power calculation, 418 BC survivors will be recruited from 10 low-income communities in Shanghai. All subjects will be randomly assigned either to the MBSR program or to a waitlisted usual care regimen that will offer the MBSR program after the completion of the other trial arm (after 6 months follow-up). Our 8-week MBSR intervention program will provide systematic training to promote stress reduction by self-regulating arousal to stress. Assessments will be made at baseline, 4 weeks (in the middle of the first MBSR intervention), 8 weeks (at the end of the first MBSR intervention), 6 months, and 12 months, and will include measures of psychological symptoms (depression, anxiety, and perceived stress), quality of life, and medication adherence. The expected outcome will be the improvement in psychological symptoms, quality of life, and medication compliance in the MBSR intervention group.

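### Two recruitment targets, 418 and 429, are given for the same power calculation, and neither leaves the required 390 after 10% attrition

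*Protocol article*

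**What the plan says.** The Sample size section takes a difference on the SF-36 physical aggregate from an earlier MBSR study ("50.3 among MBSR subjects vs. 46.9 among the control group") and reports that the two-group design with three follow-ups "needs 195 participants for each of the two groups, i.e., 390 subjects in total". It then allows for drop-out ("Assuming an attrition rate of 10" per cent) and defines the term: "attrition rate here means the percent of people who drop out from the study due to moving away, death, etc". From these inputs it states: "we concluded that we need to recruit a sample of 429 BC survivors at baseline".

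The Methods paragraph of the abstract gives a different figure and attributes it to the same source: "Based on our power calculation, 418 BC survivors will be recruited from 10 low-income communities in Shanghai".

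The section gives no standard deviation, significance level, power or within-person correlation for the 390.

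**The concern.** There are two separate problems.

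- **Contradiction.** The abstract and the Sample size section each present their number as the outcome of the power calculation for the main trial, and the numbers differ by 11. The separate pilot does not explain the gap, because the Pilot study section gives it its own 20 women.
- **Wrong inflation.** When attrition is a percentage of those who enter, the required number has to be divided by the retained fraction. Multiplying by one plus the rate falls short.

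The enrolment target is the number against which recruitment is judged. If the trial enrolled exactly 418, it would meet the abstract's target and miss that of the Sample size section. The Randomization section also allocates only once the full list of registered patients is available, so the planned length of that list should be unambiguous. The Discussion names high attrition as a threat to internal validity, which is a further reason to compute the allowance correctly.

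**Working it through.** **Inputs, all from the protocol article**

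- Required number: 390 in total, 195 per group (Sample size)
- Attrition: 10%, as a percentage of those who enter (Sample size)
- Stated targets: 429 (Sample size) and 418 (abstract, Methods)

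**Step 1. Reproduce the stated 429.** Multiplying by one plus the rate: 390 × (1 + 0.10) = 429. This matches exactly, so it is evidently how the figure was obtained.

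**Step 2. Apply the attrition as defined.** The number to recruit is N = n/(1 − d) = 390/0.90 = 433.3, rounded up to 434, or 217 per group. Check: 434 × 0.90 = 390.6.

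**Step 3. Try to reproduce 418.** From 390 and 10%, multiplication gives 429 and division gives 434. Neither gives 418. Working backwards, 418/1.10 = 380, but no 380 appears in the article, so the origin of 418 is unknown.

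**Step 4. Compare what each target retains.**

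| Recruited | Retained at 10% loss | Against 390 | Largest attrition that still leaves 390 | Below 434 by |
|---|---|---|---|---|
| 418 | 418 × 0.90 = 376.2 | about 14 short | 1 − 390/418 = 6.7% | 16 (3.7%) |
| 429 | 429 × 0.90 = 386.1 | about 4 short | 1 − 390/429 = 9.1% | 5 (1.2%) |
| 434 | 434 × 0.90 = 390.6 | met | 1 − 390/434 = 10.1% | – |

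**Step 5. Effect on power.** The article does not give the inputs for this, so the calculation is conditional. Assume that 390 was sized for planned power *p* in a two-sided 5% comparison of two means at one time point. With *N* retained, power is then Φ[(1.960 + z_p) × √(N/390) − 1.960].

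| Planned power (assumed) | N = 386.1 (from 429) | N = 376.2 (from 418) |
|---|---|---|
| 80% | 79.6% | 78.6% |
| 90% | 89.7% | 88.9% |

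The loss is 0.3 to 0.4 points with 429 and 1.1 to 1.4 points with 418. The standard deviation cancels, so only the assumed power, significance level and single-comparison simplification matter. The 390 itself could not be reproduced from what is stated, and the finding does not depend on it.

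**The case against.** The strongest reply is that little is at stake. The gap between 429 and 434 is 5 women, and attrition of 9.1% instead of a round 10% would close it. The power loss is under half a point with 429 and under one and a half points with 418. The abstract is only a summary. The Sample size section shows a derivation that does lead to 429, so a reader has good grounds to treat 429 as the working figure. It can also be said that the Statistical methods section plans a random-effects repeated-measures analysis, in which a woman who leaves after the 4- or 8-week visit still contributes data. On that view, 386 and 376 count completers and not necessarily women analysed.

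Much of this stands as to size. The inflation error alone would be minor, and the power figures are conditional. It would also be too strong to say that recruitment staff could not work out which number to use.

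Two things remain. First, the article itself inflates 390 for drop-out, so it treats 390 as the number to be retained. A mixed model's use of partial data does not change that allowance or make 390 × 1.10 the right way to obtain it. Second, the better traceability of 429 does not remove 418, which is also presented as resting on the power calculation and has no derivation anywhere in the article.

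**Conclusion.** The concern holds. The article states two enrolment targets for one trial, 11 apart (11/429 = 2.6%), and 418 does not follow from the stated inputs. Under the article's own definition of attrition, neither target retains 390: 429 falls about 4 short and 418 about 14 short, and the consistent figure is 434. These results need only the stated 390, the 10% and the definition of attrition.

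The statistical consequence is slight, at most about 1.4 points of power under the assumptions set out above. The reason to correct it is that the enrolment target is a basic figure of the trial and is contradicted within the same document.

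**What to change.** State one recruitment target in the abstract and in the Sample size section, by either route:

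- **Keep 390 and 10%.** Write 390/0.90 = 433.3, giving 434 (217 per group), in both places. This is the cleaner choice, because it follows from inputs already stated.
- **Keep 429 or 418.** State that number in both places, with the retained number it implies (386 or 376) and the resulting power. This requires giving the significance level, standard deviation, correlation and planned power behind the 390. If 418 is kept, its derivation must also be supplied.

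The second route costs wording and a recalculation. The first adds 5 women to 429, or 16 to 418. It fits the class plan in the Intervention section if the 8 to 10 groups are those of the immediate arm: 217/8 = 27.1 and 217/10 = 21.7, both within the planned 20 to 30 per class. The Trial status section says that the trial had not begun, so either change can be made before recruitment.
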